### Registration

This experiment is also registered in the open science framework (registration number: DOI 10.17605/OSF.IO/YZE5C) and https://www.clinicaltrials.gov/ (registration number: NCT05398978, date: 26/05/2022).

### Recruitment of the participants

The FWAs register all the pregnant mothers of their respective unions in the traditional paper-based system. We will digitalize an e-registration system in the intervention areas and in the control areas we will continue the paper-based register. The Family Planning Inspectors (FPI) then collate the data and a complete list of pregnant mothers at the sub-district level is formed.

The flow diagram of pregnant mothers’ enrolment from the FWA register is given in **Fig 2**. We will take the list of all the existing pregnant mothers from the paper-based FWA register who will be in their 28–36 weeks of pregnancy during the first 15 days of the baseline period of both the intervention and control areas. Then we will invite all the pregnant women from that list of the intervention arm to be registered in the e-Registration system. The FWAs will register the consenting pregnant women to the digital system. The registered pregnant women in the e-Registration system will then receive mHealth service from the midwives. In the control arm, we will invite all the eligible pregnant women to take part in the study and enroll the pregnant women who will give consent.

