## Abstract

Despite substantial progress, Bangladesh still has a high rate of maternal deaths owing to difficulties during pregnancy, delivery, and the postpartum period. Increasing facility delivery is mandatory to reach the goal of bringing down the MMR to <70 deaths/100,000 live births by 2030. In the era of digitalization, the introduction of e-registration and mHealth may aid the government in reaching this target. The southern part of Bangladesh is a hazard-prone area, where service uptake from institutions is low. This study aims to determine the effect of an e-registration tracking system and mHealth counseling on institutional deliveries to pregnant mothers in hazard-prone areas of southern Bangladesh. We will conduct an open-label, two-arm, non-randomized controlled cluster trial for six months and use three hazard-prone areas for intervention and another three hazard-prone areas for control. We will collect data at baseline and end-line of the study period using a structured questionnaire. We will enroll at least 268 pregnant mothers from the intervention and 268 pregnant mothers from the control areas after screening based on the inclusion and exclusion criteria. Pregnancy information will be obtained from the Family Welfare Assistant register. The respondents of the intervention arm will be registered in the e-Registration system, and receive voice call and text messages from the midwives to have their deliveries done in healthcare facilities. We will follow the participants until their delivery and exclude those respondents from the study who will have post-dated delivery, migrate out, lost to follow-up, or die during the study period. Random-intercept mixed-effect logistic regression will be performed to explain the relationship of e-registration and mHealth package with institutional delivery. Institutional delivery is still uncommon in Southern Bangladesh despite several interventions. Innovative approaches like e-registration and mHealth counseling may be helpful to bring women to health facilities. The findings from the study might enable the policy makers of Bangladesh to integrate the intervention package into the existing healthcare system. This experiment is registered in the open science framework.

**Clinical trial registration:** Registration number: DOI 10.17605/OSF.IO/YZE5C) and https://www.clinicaltrials.gov/ (registration number: NCT05398978.

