### Exclusion criteria

Pregnant mothers with severe pregnancy-related complications at the baseline,Pregnant mothers who will develop severe pregnancy-related complications, migrate out, lost to follow-up, or die during the study period,Mothers who will deliver beyond 42 weeks of their gestational period,Pregnant mothers who will refuse to participate in the study.

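### Women enter the intervention arm by accepting e-registration but enter the control arm by accepting the study: an extra gate in one arm only, with a bias whose size depends on an unknown decline rate

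*Protocol article*

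**What the plan says.** The relevant text of the protocol article is under Recruitment of the participants, with supporting statements elsewhere.

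- **Common frame.** "We will take the list of all the existing pregnant mothers from the paper-based FWA register", restricted to 28–36 weeks, in both areas.
- **Intervention areas.** "Then we will invite all the pregnant women from that list of the intervention arm to be registered in the e-Registration system". Next, "The FWAs will register the consenting pregnant women to the digital system". Then, "The registered pregnant women in the e-Registration system will then receive mHealth service from the midwives".
- **Control areas.** The team says "we will invite all the eligible pregnant women to take part in the study and enroll the pregnant women who will give consent".
- **Abstract.** "The respondents of the intervention arm will be registered in the e-Registration system, and receive voice call and text messages from the midwives".
- **Shared rules.** The exclusion criteria remove "Pregnant mothers who will refuse to participate in the study" in either arm. Ethics approval requires written consent before data collection. The inclusion criteria require access to a mobile phone in both arms and differ between arms only by residence.

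No section describes follow-up of intervention-area women who decline e-registration, or an equivalent request put to control women.

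**The concern.** E-registration is not just administration. The Objectives and Intervention sections make it the first half of the package being evaluated. As the recruitment text stands, belonging to the intervention arm means having accepted part of the treatment, while belonging to the control arm means having agreed to be studied.

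Two consequences follow.

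- **Bias.** If women who decline tracking are also less inclined to deliver in a facility, they leave the intervention denominator but their counterparts stay in the control denominator. The Data collection process section itself treats place of delivery as largely the woman's choice, since it excludes certain deliveries for not depending on that choice. The trial is open-label and non-randomized, and area allocation is known before anyone is invited, so nothing in the design balances this selection. It would come on top of any difference between the two districts.
- **Target of the estimate.** The Introduction and Discussion aim at roll-out. That decision needs the effect of offering the package to all eligible women. An arm made up of acceptors estimates the effect among acceptors.

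This is an enrolment rule, so it cannot be left to the analysis. If decliners are never enrolled, no end-line data exist for them.

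**Working it through.** **1. The plan's own figure.** Under Sample size, p1 = 53.8, p2 = 68.5, z-values 1.96 and 0.85, design effect 1.50, non-response 5%:

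- [53.8 × 46.2 + 68.5 × 31.5] / 14.7² = 4643.31 / 216.09 = 21.488
- 21.488 × (1.96 + 0.85)² = 169.7
- 169.7 × 1.5 = 254.5
- 254.5 / 0.95 = 267.9, so 268 per arm

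The stated 268 reproduces. The point does not depend on it, but it supplies the 53.8% reference rate and the 14.7-point target effect used below.

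**2. Entry conditions side by side.**

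| Step | Intervention areas | Control areas |
|---|---|---|
| On paper FWA register | yes | yes |
| Phone access | yes | yes |
| Study consent; refusers excluded | yes | yes |
| Accepts e-registration | yes, as written | not asked |

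The first three rows are common to both arms. Only the last differs.

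**3. Illustrated size.** The documents give neither an e-registration decline rate nor a delivery rate for decliners, so both are assumed here. Let d be the proportion declining, r their facility-delivery rate, and 53.8% the rate among all women otherwise eligible in both areas, with no true effect. Then

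rate among acceptors = (0.538 − d × r) / (1 − d).

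| d | r | Acceptors' rate | Spurious gain (points) | Share of 14.7 |
|---|---|---|---|---|
| 5% | 40% | 0.518/0.95 = 54.5% | +0.7 | 5% |
| 5% | 30% | 0.523/0.95 = 55.1% | +1.3 | 9% |
| 10% | 40% | 0.498/0.90 = 55.3% | +1.5 | 10% |
| 10% | 30% | 0.508/0.90 = 56.4% | +2.6 | 18% |
| 20% | 40% | 0.458/0.80 = 57.3% | about +3.5 | 23% |
| 20% | 30% | 0.478/0.80 = 59.8% | about +6.0 | 40% |

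The control arm is held at 53.8%, so d must be read as the decline beyond ordinary study refusal, which affects both arms.

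**4. Effect on the test.** Use an effective size per arm of 268 × 0.95 / 1.5 ≈ 170, a nominal two-sided 5% test, no true effect, and SE = √[(a(1 − a) + 0.538 × 0.462)/170], where a is the acceptors' rate. The rejection probability is then about 5.1% for a spurious gain of 0.5 points, 6.6% for 2.0 points, 11.5% for 4.0 points and 20% for 6.0 points.

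**The case against.** The strongest reply is that the article never states that a woman who declines e-registration leaves the study. The inclusion and exclusion lists do not mention e-registration, and the refusal criterion concerns refusal of the study. The word for consent in the recruitment text could mean one joint study consent. The enrolment flow diagram (Fig 2) is not shown and might settle this. That leaves room for doubt but does not close the gap. Even under a joint consent, intervention-area women are asked to accept something that control women are not. With the Abstract, the recruitment text still gives a decliner no way into the arm.

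The second reply is that the hurdle is low. Every listed woman is already on the FWA's paper register, and e-registration means the same type of worker entering her on a tablet at a home visit. This stands: the decline rate may well be small. The only related figure in the protocol is 5% non-response, which is not an e-registration decline rate. At that level the spurious gain is about 1 point.

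The third reply is that the baseline questionnaire records preferred delivery place, health-seeking behaviour, beliefs and distance, and that inference rests on an adjusted odds ratio. This also stands in part. Adjustment for these items, if they are in the model, would remove some of the bias, as far as they capture willingness to be tracked.

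A reader might go further and infer that women must accept midwife contact to enter, or that registered women whom the midwives never reach are dropped. Neither is in the text. mHealth follows registration, the Intervention section provides for repeated call attempts, and no rule removes a registered woman for not being reached. Only refusal of e-registration is at issue.

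**Conclusion.** The point holds on the wording. Acceptance of the first intervention component is an entry gate in the intervention arm alone, and the shared consent and refusal rules do not remove it. The likely direction favours the intervention, but only on the assumption that decliners are less inclined to facility delivery, which no section shows. On the assumed values the spurious gain runs from under 1 point at 5% decline to about 6 points at 20%, and it is negligible if nearly everyone accepts. The upper end is the corner of an assumed grid, not an expected value.

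It might be tempting to call the result unusable for the roll-out decision. The documents do not support that. An effect among acceptors can be interpreted, but it answers a narrower question than the effect of offering the package to all eligible women. What makes the change worth making before enrolment is that later analysis could not fully undo the selection, while preventing it is cheap.

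**What to change.** Rewrite Recruitment of the participants, and align the Abstract with it:

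1. Use one identical step in both arms: from the paper FWA list, obtain study consent and complete the baseline interview before e-registration is offered.
2. Keep every consenting Chandpur woman in the intervention arm for the primary analysis, whether or not she accepts e-registration.
3. Report the numbers listed, approached and consented in each arm, and the number e-registered in the intervention arm.

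The cost is reordered field steps, revised consent wording, and some dilution by non-uptake. If 14.7 points is taken as the effect among acceptors and decliners gain nothing, the expected difference is 14.7 × (1 − d): about 14.0 points at 5% decline, 13.2 at 10% and 11.8 at 20%. The dilution is therefore slight if few decline. The stated 268 per arm is a minimum, so the protocol already allows more women to be enrolled.

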**Fig 2 pone.0271364.g002:**
[figure not shown]
Flow diagram of pregnant mothers enrolment from FWA register.

The inclusion and exclusion criteria of the participants are given in the following:

### Inclusion criteria

Pregnant mothers registered in the paper-based FWA register,Age group 19–45 years,Residence of—Intervention group: Chandpur Sadar, Faridganj, or Kachua sub-districts of Chandpur District, and Control group: Bhola Sadar, Charfesson, or Lalmohan sub-districts of Bhola District,Gestational period of 28–36 weeks,Have access to a mobile phone.

### Exclusion criteria

Pregnant mothers with severe pregnancy-related complications at the baseline,Pregnant mothers who will develop severe pregnancy-related complications, migrate out, lost to follow-up, or die during the study period,Mothers who will deliver beyond 42 weeks of their gestational period,Pregnant mothers who will refuse to participate in the study.

### Sample size

We have planned to recruit and then follow up a minimum of 268 pregnant mothers in the intervention areas and 268 pregnant mothers in the control areas. According to a study conducted in Ethiopia, the implementation of mHealth services using both voice calls and text messages increased facility delivery by 14.7% in the intervention group compared to the control group (43.1% compared to 28.4%; AOR: 1.98 (95%CI: 1.53, 2.55)) [4]. We decided on this proportion we need to determine the number of respondents for our study at a 5% level of error margin and 80% power. Using the formula below we determined the sample size to be 268 for each of the intervention and control groups.

$$n=\frac{p_{1}(100-p_{1})+p_{2}(100-p_{2})}{{\left(p_{1}-p_{2}\right)}^{2}}x{\left(z_{\alpha }+z_{\beta }\right)}^{2}x\;g$$

-----------------------------------------

Here,

p_1_ = 53.8% (Proportion of institutional delivery in Bangladesh) [19]

p_2_ = 68.5% (Proportion of institutional delivery following intervention assuming a 14.7% increase) [4]

z_α_ = 1.96 (at 5% error margin)

z_β_ = 0.85 (at 80% power)

g = 1.50 (design effect)

non-response rate = 5%

-----------------------------------------

      **n = 268**

Based on the logic, we anticipate that the sample size will have enough statistical power to meet the primary objective of our study.

### Data collection process

**Fig 3** provides the conceptual framework of data collection process. We will use a structured questionnaire developed in Bangla for data collection at the baseline and end line of the study period. Two local recruits at each of the intervention and control areas will be employed for data collection to avoid any issues with the local dialect. Among the two data collectors, one will be a female who will collect data from the pregnant mothers directly for the cultural issue and the nature of the questions asked, and another will be a male who will support the female data collector during community visits. We will train the data collectors on the questionnaire, data collection method, ethics, and infection prevention and control measures considering the COVID-19 context according to the WHO standards.

**Fig 3 pone.0271364.g003:**
[figure not shown]
Conceptual framework of data collection process.

The questionnaire is subdivided into three main sections–screening measure, baseline survey, and end-line survey. During the baseline period, we will screen pregnant mothers using the screening tools. The screening tools will include mothers who will give consent and exclude pregnant mothers with severe pregnancy-related complications, such as eclampsia, antepartum hemorrhage, sepsis, and/or COVID-19 infection. The baseline section is designed to collect data of the respondents about the socio-demographic information, pregnancy-related information, such as parity, gravida, months of pregnancy at the first antenatal visit, counseling on facility visit, birth preparedness plan, knowledge on danger signs, location, and outcome of previous pregnancy and existing comorbidities, and other information such as personal belief, social norm, choice of delivery place, health-seeking behavior in general, and the distance between the respondent’s home, and the nearest healthcare facility. It will take approximately 20 minutes to complete the baseline section of the data collection tool. The pregnant mothers will then be followed-up until their delivery. Then their delivery-related data, such as place of delivery, mode of delivery, and the delivery outcome, will be collected at the end line of the study period using the relevant section of the questionnaire, which will take about 10 minutes to fill up.

Since the baseline, the end line data collection will be done at the end of the fourth month of the study period. The baseline and end-line data collections will be done by face-to-face interviews. The questions will be read out to the participants and the data collectors will fill up the questionnaire with the information given by the mothers. The mothers who will have post-dated delivery, develop severe pregnancy-related complications, will be lost to follow-up, or die during the study period will be excluded from the study. We will exclude post-dated deliveries and mothers with severe pregnancy-related complications as, by nature of the emergence, these deliveries are conducted in the healthcare facility and do not depend on the choice of the respondent.

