### Intervention

#### e-registration and mHealth

In the intervention areas, the pregnant mothers will be registered in the FWA e-Register database so that they can be tracked and their schedules can be maintained electronically. The FWAs will visit the pregnant mothers’ homes of their designated unions and register them in the eMIS database using an android tablet computer. eMIS software will be used in the android tablet computer to capture the data. Both online and offline data input can be done and the offline data will be automatically synced to the central database once going online. The FPIs will perform data quality checks, approval, and monthly aggregation of union-level data to the sub-district levels. The aggregated list will be sent to the midwives. Then the midwives will call and send text messages to the pregnant mothers whose expected delivery dates are nearby and counsel them to conduct their deliveries at the healthcare facility. The midwives will call three times in case of a failure of the first two attempts to reach each participant of the intervention arm. The text messages will be tailored beforehand in Bangla and the midwives will be trained on how to counsel the pregnant mothers on facility delivery. Following e-Registration, the mHealth intervention will be given once to the pregnant mothers of the intervention arm during 28–36 weeks of their pregnancy. We expect to evaluate the combined effect of e-Registration tracking and mHealth counseling through this study.

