### Quality control and quality assurance

We do not anticipate any major deviation from the protocol such as any harm to the participant, or enrollment of participants not eligible for the study. Minor deviations like lost to follow-up will be addressed by enrolling an adequate sample size taking into consideration at an attrition level of 5%. We will communicate with the Ethical Review Board, and trial registries if any major and/or minor deviation occurs during the trial. The data monitoring committee will regularly check data and monitor it to maintain the data quality. An expert will double-check the validation of data collected by the data collectors. The data entry team will link records that have been collected with the help of individual identifiers assigned. We will remove this identifying information once the records are done matching. The anonymized data will be uploaded to a central web-based platform regularly, after following all the appropriate confidentiality requirements. We will use an encrypted, password-protected centralized database system to store data, and only authorized members of the research team will be allowed access.

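### The primary outcome is the mother's own report, given at an open-label interview after only one arm was counselled toward facility delivery; no second source is described, so over-reporting that differs by arm could be counted as effect

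*Protocol article*

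**What the plan says.** The Primary outcome section counts a birth as institutional when two conditions are met together: it took place in a healthcare facility at the study sites, and a trained provider conducted it.

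The Data collection process section says how this is learned. Where and how the birth took place, and its result, are asked at end line, at the end of the fourth month. The interview is face to face, and "the data collectors will fill up the questionnaire with the information given by the mothers". On staffing, "Two local recruits at each of the intervention and control areas will be employed for data collection"; the reason given is local dialect.

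Study design and setting makes the trial open-label, puts the two arms in different districts, and states that the e-registration and mHealth services do not exist in the control district. In the intervention arm, midwives call and text the women and "counsel them to conduct their deliveries at the healthcare facility".

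Two other places bear on the point. Quality control and quality assurance says "An expert will double-check the validation of data collected by the data collectors", and that identifying information is removed once records have been matched. The Discussion acknowledges possible recall bias because of the four-month gap.

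**The concern.** The intervention consists of advice to deliver in a facility, and the primary outcome is the mother's answer to whether she did. One arm has had that advice from the trial and the other has not. A mother who was counselled and then delivered at home has a reason to give the advised answer that a control mother has less of. Interviewer and arm also coincide, so any difference in how interviewers probe or record is confounded with treatment.

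Recall bias is a different matter: nothing about a four-month gap makes it act in one arm only. Reporting toward the advised answer acts in the direction of the hypothesis. The planned model does not protect against it. Unions lie wholly within one arm, so a random intercept for union describes variation between unions within arms, and a shift shared by a whole arm goes into the intervention odds ratio. A larger sample would only estimate the biased quantity more precisely.

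**Working it through.** **Inputs.** From the Sample size section: control proportion "53.8% (Proportion of institutional delivery in Bangladesh"), intervention proportion "68.5% (Proportion of institutional delivery following intervention assuming a 14.7% increase"), z for alpha "1.96 (at 5% error margin"), z for power "0.85 (at 80% power"), design effect 1.50, non-response 5%. The documents give no misreporting rate, so the rate r below is an assumption shown over a range.

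**Step 1: reproduce the plan's own figure.**
- Variance term: 53.8 × 46.2 + 68.5 × 31.5 = 2485.56 + 2157.75 = 4643.31.
- Divided by 14.7² = 216.09: 21.488.
- Times (1.96 + 0.85)² = 7.8961: 169.67.
- Times 1.5: 254.51.
- With 5% non-response: 254.51 / 0.95 = 267.9, or 254.51 × 1.05 = 267.2. Both round up to the stated 268 per arm.

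The sample size is not in question.

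**Step 2: size of the spurious difference.** Let p be the true proportion in both arms (no effect). Let r_I and r_C be the fractions of non-facility births reported as births in a facility with a trained provider. The observed difference is then

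(1 − p) × (r_I − r_C).

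Only the net rate r = r_I − r_C matters. With p = 0.538, so 1 − p = 46.2%:
- r = 5%: 0.05 × 46.2 = 2.3 points; 2.31 / 14.7 = 16% of the target.
- r = 10%: 0.10 × 46.2 = 4.6 points; 4.62 / 14.7 = 31% of the target.

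If 10% of intervention and 5% of control non-facility births were misreported, the net rate would be 5% and the bias 2.3 points, not 4.6.

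**Step 3: chance of a false significant benefit.** The test is a two-proportion normal test at 1.96, with effective size per arm 268 × 0.95 / 1.5 = 169.7. For r = 10% the observed proportions are 0.538 and 0.5842:
- standard error under the null: √(0.5611 × 0.4389 × 2 / 169.7) = 0.0539, so the critical difference is 0.1056;
- standard error at the observed proportions: 0.0538;
- probability: Φ((0.0462 − 0.1056) / 0.0538) = Φ(−1.10) ≈ 13%.

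| Net r (assumed) | Spurious difference | Odds ratio | False significant benefit |
|---|---|---|---|
| 0% | 0 | 1.00 | 2.5% |
| 5% | 2.3 points | 1.10 | 6% |
| 10% | 4.6 points | 1.21 | 13% |
| 20% | 9.2 points | 1.47 | 41% |

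The smallest significant difference is about 10.5 points, which needs r of about 10.5 / 46.2 = 23%. The whole 14.7-point target needs 14.7 / 46.2 = 32%.

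**Step 4: a lower base rate.** The Introduction puts service uptake in the south about 11% below the national estimate. Reading that as percentage points of facility delivery (an assumption), p is 42.8%. The same 5% and 10% then give 2.9 and 5.7 points, and r = 10% gives a false significant benefit about 18% of the time.

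**The case against.** There is a fair case on the other side.

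- **Over-reporting is not shown.** A reader might infer that intervention mothers will over-report. No passage says so and no rate is given. Place of birth is a concrete and recent event, counselling is given once, and the midwives who counsel are not the interviewers. This stands: the point is a risk.
- **Controls may over-report too.** The baseline questionnaire asks about counselling on facility visits and choice of delivery place in both arms, so controls are also alerted to the topic and may have had routine advice. This stands: only the net rate biases the result, and the illustration sets control over-reporting to zero.
- **A false claim about the attendant alone changes nothing.** A reader might count any wrongly claimed skilled attendant. The outcome requires a facility as well, so a home birth with a falsely claimed attendant is still non-institutional.
- **The article is condensed.** A reader might infer that no verification exists, or that misreporting could never be detected. The end-line items and Fig 3 are not shown, and the method of the expert check is not given. Likewise, the protocol never states whether interviewers are masked; that they know the arm is inferred from the open-label design and area-based recruitment. What remains is that the article does state its measurement rule, the mother's answer, and names no other source. The expert check, as worded, concerns the collectors' data.
- **At 5 to 10% the bias would seldom produce significance on its own.** True, as step 3 shows. It would still inflate the estimate offered to policy makers.

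**Conclusion.** The point holds as a risk of directional bias in a stated measurement rule. It is not a contradiction or an arithmetic error. The primary outcome is the mother's report at an open-label interview by area-specific interviewers, after trial counselling in one arm only. No second source is described, and the only reporting problem acknowledged is recall.

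The figures of 2.3 and 4.6 points rest on four assumptions: no true effect, 53.8% in both arms, no over-reporting by controls, and a net 5% or 10% of intervention-arm non-facility births falsely reported as births in a facility with a trained provider. Any over-reporting by controls reduces them; a lower base rate raises them. The change should be made before end-line data collection, because identifiers are later removed and reported births could then no longer be traced. Confidence is medium, since the true rate is unknown.

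**What to change.** At the existing end-line interview, identically in both arms:

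1. Record the facility name, the delivery date and the attendant.
2. Ask to see the discharge slip or birth record, and record whether it was seen.

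In the analysis:

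3. Report, for each arm, the proportion of reported facility deliveries confirmed by document.
4. Add a sensitivity analysis of the primary outcome that counts only document-confirmed facility deliveries. State with it that availability of documents may differ between the two districts, so this analysis can carry its own differential error.

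The primary definition, design and sample size stay as they are. The cost is about a minute (an estimate) on an interview planned at about 10 minutes, plus one analysis. The downside is that some genuine facility births will have no paper to show, which is why the documented count should not replace the primary definition.

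Comparison with facility registers is optional. The outcome covers any facility at the sites across six sub-districts, so this needs access and fieldwork and is more than a redirection of the planned expert check. If it is done, it should cover the same fraction of reported facility deliveries in both arms and take place before identifiers are removed.
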